## Abstract

**Background:**

Stroke is one of the leading causes of long-term disability and is frequently associated with persistent motor, cognitive, emotional, and social sequelae that affect autonomy and quality of life. Music-based interventions have shown potential benefits in post-stroke rehabilitation, particularly through rhythmic auditory stimulation, structured instrumental practice, and active musical engagement. These approaches may support motor coordination and motivation and may also contribute to emotional regulation, social interaction, and perceived quality of life. However, evidence remains limited regarding structured music-based interventions that integrate motor activities with broader cognitive and psychosocial components into post-stroke rehabilitation. This randomized waitlist-controlled intervention study aims to evaluate the effects of a structured music-based intervention on motor function after stroke, with executive functioning and stroke-specific quality of life being examined as exploratory outcomes.

**Methods:**

A prospective, phased, randomized waitlist-controlled intervention study will include adults aged 18–70 years who have experienced a stroke at least 3 months before enrollment. The first recruitment phase will be conducted in a single outpatient neurological rehabilitation center in the Community of Madrid, Spain, with subsequent recruitment phases planned at additional outpatient neurological rehabilitation centers within the Community of Madrid until the required sample size is achieved. Two groups will be formed: an experimental group receiving standard rehabilitation care plus a structured music-based intervention consisting of 10 sessions and a waitlist group receiving only standard rehabilitation care during this period, followed by the structured music-based intervention. Assessments will be carried out at week 0 (baseline), week 5 (post-intervention), and week 10 (after group crossover), with an additional follow-up at 3 months. The primary outcome will be motor function. Upper-limb motor function will be assessed as a secondary motor outcome, while executive functioning and stroke-specific quality of life will be examined as exploratory outcomes. Analyses will follow the intention-to-treat principle, with additional analyses conducted for participants completing at least 80% of sessions. A linear mixed-effects model will be used to estimate the main effect of the intervention on the primary motor outcome, with additional secondary and exploratory models performed for upper-limb motor function, executive functioning, and stroke-specific quality of life. The model will include time, group, and the interaction between group and time as fixed effects, with time since stroke included as a covariate. Additional analyses will be conducted using intraclass correlation coefficients to explore the agreement between participant and family member reports of executive function.

**Discussion:**

This protocol will evaluate a structured music-based intervention as a complement to standard rehabilitation care, with a primary focus on motor rehabilitation. Exploratory analyses will examine whether the intervention is associated with changes in executive functioning and stroke-specific quality of life. The study is expected to provide preliminary evidence on the feasibility and potential effects of this integrative music-based intervention within post-stroke rehabilitation and to contribute to the development of multidomain rehabilitation approaches. The findings may inform the design of future studies and the potential implementation of music-based interventions in post-stroke rehabilitation settings.

**Study protocol preregistration:**

https://osf.io/hqruw.

## Introduction

Stroke is one of the leading causes of long-term disability and comprises ischemic and hemorrhagic subtypes (1). In addition to the acute phase, stroke survivors often experience persistent sequelae that compromise autonomy, participation, and quality of life (2, 3). Motor impairments, executive dysfunction, and deterioration of emotional and social wellbeing are among the most relevant consequences of stroke. These areas represent fundamental aspects of post-stroke rehabilitation and therefore constitute the core focus of this protocol (4).

Post-stroke neurorehabilitation is increasingly understood as a multidimensional and multidisciplinary process that should address not only body functions but also activity, participation, and quality of life (4, 5). However, standard rehabilitation approaches often address motor, cognitive, and emotional domains separately, which may limit their ability to capture the dynamic interaction between these domains in everyday functioning. Cognitive impairments may reduce engagement in motor training, while emotional disturbances can exacerbate functional limitations and negatively affect recovery trajectories (4, 6, 7). Integrative rehabilitation approaches may therefore provide added value by promoting coordinated stimulation across domains and by increasing the functional relevance of rehabilitation tasks.

Within this context, music-based interventions represent a potentially valuable complementary approach in post-stroke rehabilitation due to their multisensory, rhythmic, motivational, and socially engaging nature. Over the past two decades, multiple studies have explored music-based interventions in post-stroke rehabilitation, primarily focusing on isolated domains such as motor recovery, cognitive function, or emotional wellbeing. Evidence from randomized controlled trials has shown that rhythmic auditory stimulation can enhance gait and upper-limb coordination, while structured instrumental practice supports fine motor skills and functional recovery mechanisms (8, 9). Other studies have emphasized the cognitive and emotional benefits of music-based interventions, highlighting improvements in executive functions, attention, and mood regulation (10, 11). Moreover, systematic reviews have indicated that participation in active musical activities contributes to social engagement and perceived quality of life by reducing symptoms of depression and anxiety and promoting self-efficacy and motivation during rehabilitation (12–14).

Despite this growing body of evidence, most existing interventions target these domains separately, focusing either on motor outcomes or on emotional and cognitive aspects, without fully integrating them into a single, comprehensive rehabilitation model. Although multidomain rehabilitation models are beginning to emerge in stroke care, structured music-based intervention protocols specifically designed to integrate motor rehabilitation with exploratory executive and quality-of-life-related components within a single coherent intervention remain limited (11, 14, 15). The present study seeks to address this gap by evaluating a structured music-based intervention primarily focused on motor rehabilitation while also exploring potential changes in executive functioning and quality of life as broader rehabilitation-related outcomes.

From a motor perspective, participants frequently present with hemiparesis, loss of coordination, and limitations in fine motor skills, which interfere with activities of daily living. Despite standard rehabilitation care, motor recovery is often incomplete, prompting the search for complementary strategies to support mechanisms associated with motor relearning and functional recovery (2). Evidence suggests that music, particularly through rhythmic auditory stimulation and structured musical engagement, can support motor and cognitive recovery processes (8, 9, 14). In addition, rhythmic auditory stimulation has been shown to improve gait synchronization (16), while instrumental practice may enhance bimanual coordination and fine motor function (17). Clinical trials have demonstrated that exercises using simple instruments or electronic keyboards improve manual dexterity and motor precision, in addition to boosting motivation and adherence to treatment (8, 13, 18). A recent systematic review has reported beneficial effects of music therapy interventions on hand function in patients with stroke (9). These findings support the inclusion of rhythmic and instrumental tasks in this protocol as a complementary strategy to support motor rehabilitation.

With regard to executive functions, many participants exhibit deficits in attention, working memory, planning, and cognitive flexibility, which have a direct impact on behavioral organization and adaptation to daily life (6, 7, 11). Clinical observations and case-based reports further illustrate the presence of these impairments in post-stroke populations (19). Recent studies have suggested that active music practice may engage networks involved in auditory–motor integration and cognitive control (10, 20), facilitating attentional regulation, inhibition of automatic responses, and the ability to switch strategies. Structured musical activities, such as following rhythmic patterns, improvising, or coordinating musical sequences, have been used to target executive processes, with emerging evidence of cognitive benefits (21). A recent review has also highlighted the potential of music-based interventions to improve executive function and emotional wellbeing after stroke (11). The proposed program incorporates structured musical activities requiring planning, working memory, and cognitive flexibility, with the aim of increasing cognitive engagement during motor and musical tasks.

Post-stroke quality of life is affected not only by physical and cognitive limitations but also by the high prevalence of emotional disorders such as depression and anxiety. These conditions significantly reduce social participation and adherence to treatment (3, 19). Research indicates that daily music listening can improve mood and perceived wellbeing (16). Moreover, participation in active group sessions fosters social interaction and reduces feelings of isolation (13). Participation in music-based activities may support social engagement and emotional wellbeing after stroke (13, 14). Some programs have reported improvements in stroke-specific quality-of-life scores, demonstrating that music provides benefits beyond the motor domain (14). This protocol includes a group-based, integrative format designed to harness these positive effects on quality of life and emotional wellbeing.

Taken together, the available evidence suggests that music acts as a multisensory and motivating stimulus capable of influencing motor function (8, 16), cognition (11, 21), and emotional wellbeing (11, 14). Building on this rationale, this protocol proposes a ten-session integrative music-based intervention primarily designed to support motor recovery through rhythmic and instrumental tasks. The program also includes structured activities involving planning, working memory, cognitive flexibility, social interaction, emotional regulation, and motivation, which will be examined as exploratory components in relation to executive functioning and quality of life.

Although structured music-based and music-supported rehabilitation protocols have recently begun to be explored in post-stroke populations, evidence remains limited, particularly regarding integrative approaches addressing multiple rehabilitation-related domains simultaneously (22).

Accordingly, the program is presented as a structured integrative model that builds on previous evidence on music-based interventions, neurologic music therapy, and music-supported rehabilitation after stroke. The primary aim of this study is to evaluate the effects of the intervention on motor function. Executive functioning and stroke-specific quality of life will be examined as exploratory outcomes, given the brief intervention dose and the multifactorial nature of change in these domains.

## Methods and design

### Context of post-stroke rehabilitation and rationale for the intervention

Post-stroke neurorehabilitation is typically based on multidisciplinary approaches involving physiotherapy, occupational therapy, speech and language therapy, and neuropsychological interventions (4, 5). These treatments primarily focus on restoring motor function, improving communication abilities, and addressing cognitive deficits, depending on the participant’s clinical profile.

In recent years, there has been increasing recognition of the need for more comprehensive and participant-centered rehabilitation models that address not only impairments at the body function level but also activity, participation, and quality of life (4, 5). Multidisciplinary and, more recently, integrative approaches aim to combine different therapeutic modalities to enhance functional recovery and promote engagement in meaningful activities (15).

However, despite this shift toward multidimensional rehabilitation, the majority of existing interventions are still delivered in a domain-specific manner, with motor, cognitive, and emotional aspects often addressed separately across different therapeutic disciplines (6, 7). This fragmentation may limit the ability of rehabilitation programs to capture the dynamic interaction between these domains in real-life functioning.

Within this context, the proposed music-based intervention represents a potentially valuable complementary approach due to its inherently multisensory and integrative nature. Musical activities simultaneously engage motor, cognitive, and emotional processes, offering an opportunity to address these domains within a unified rehabilitation-oriented framework (11, 14).

This protocol aims to address this gap by proposing a structured music-based program primarily focused on motor rehabilitation while incorporating executive and quality-of-life-related components as exploratory domains within a single coherent intervention. The program combines rhythmic, instrumental, and structured musical activities to support motor rehabilitation while also engaging cognitive and emotional processes.

### Study design

This is a prospective, phased, randomized waitlist-controlled intervention study with a parallel-group design, aimed primarily at evaluating the effects of the intervention on motor function. Upper-limb motor function will be assessed as a secondary motor outcome, while executive functioning and stroke-specific quality of life will be examined as exploratory outcomes. Participants will be randomly allocated to either an experimental group or a control/waitlist group.

The study will be implemented in successive recruitment phases. The first phase will be conducted in a single outpatient neurological rehabilitation center in the Community of Madrid, Spain, and subsequent phases will extend recruitment to additional outpatient neurological rehabilitation centers within the Community of Madrid until the required total sample size is achieved.

In the first recruitment phase, approximately 24 participants are expected to be included, with 12 participants allocated to each group. Recruitment will then continue in subsequent phases across additional centers, maintaining the same eligibility criteria, intervention protocol, assessment schedule, randomization procedures, and outcome measures, until the planned sample of 76 participants is reached.

Two groups will undergo the same overall rehabilitation process. Over a total of 5 weeks (two sessions per week), the experimental group will receive their standard rehabilitation care complemented by a program of music-based activities. The control/waitlist group will receive only standard rehabilitation care during the first 5-week intervention period and will subsequently undergo the music-based program after the experimental group has completed it, thereby effectively switching their roles.

This design ensures that all participants benefit from the intervention while allowing temporal comparison between the groups. This structure is consistent with previous studies of similar music-based rehabilitation programs and supports ethical rigor by ensuring that all participants receive a potentially beneficial intervention.

All participants will be assessed at baseline (week 0), after 5 weeks (post-intervention), and again at 10 weeks (after crossover). A 3-month follow-up will be conducted to explore the maintenance of potential effects.

The study has been preregistered in OSF Registries.^1^ This record is reported as an open science preregistration and is not presented as a clinical trial registry.

### Recruitment

Participants will be recruited in successive phases from outpatient neurological rehabilitation centers in the Community of Madrid, Spain. The first recruitment phase will take place in a single specialized outpatient neurological rehabilitation center, where patients are typically in the late subacute or chronic phase of recovery (≥3 months post-stroke). Based on the estimated annual recruitment capacity and eligible patient flow at this center, approximately 24 eligible and recruitable participants are expected to be included during the first recruitment phase, with 12 participants allocated to each group.

Subsequent recruitment phases will extend to additional outpatient neurological rehabilitation centers within the Community of Madrid to reach the required total sample size of 76 participants. All participating centers will follow the same eligibility criteria, intervention protocol, assessment schedule, randomization procedures, and data collection methods. Recruitment will continue until the planned total sample size has been achieved, with completion of recruitment expected within approximately 1 year.

This is a non-pharmacological, music-based rehabilitation intervention. It does not involve changes to participants’ usual medical care or prescribed medication. Participants will receive written information about the study along with the informed consent form. Those who voluntarily agree to participate will be randomly assigned to the experimental or control/waitlist group.

Eligibility screening will be conducted by trained rehabilitation professionals using a medical record review, clinical interview, Barthel Index scoring, the Montreal Cognitive Assessment (MoCA), and functional screening of motor and receptive language abilities.

#### Inclusion criteria

The inclusion criteria will include the following:Participants must be between 18 and 70 years of age. The upper age limit was established to reduce heterogeneity associated with age-related comorbidities and cognitive decline, which may influence rehabilitation outcomes and engagement in structured interventions. This range is also consistent with previous research on post-stroke rehabilitation and functional recovery mechanisms (6, 7).Participants must have a stroke diagnosis made at least 3 months prior to participation, corresponding to the late subacute phase (3–6 months post-stroke) and/or the chronic phase (>6 months), in line with commonly used temporal classifications of post-stroke recovery phases (5). These classifications distinguish subacute and chronic stages based on time since stroke onset, thereby helping to ensure clinical stability and reduce variability associated with earlier stages of recovery.Participants must have sufficient cognitive and receptive language abilities to understand and follow simple instructions, regardless of verbal expression capacity. Cognitive screening will be conducted using the Montreal Cognitive Assessment (MoCA), with a score of ≥18 used as the eligibility threshold. Receptive language and task comprehension will also be confirmed during screening through the ability to follow simple one-step verbal instructions.Participants must have a minimum functional ability to perform basic activities of daily living, defined as a Barthel Index score of ≥40, together with sufficient sitting tolerance and the ability to engage in structured activities, with support if needed. Participants must have sufficient motor ability to perform the planned intervention tasks, as determined during screening through observation of seated postural control and basic upper-limb performance on intervention-related tasks.Participants must not have severe pre-stroke cognitive or functional impairments, based on medical records and clinical history.

#### Exclusion criteria

The exclusion criteria will include the following:Participants must be over 70 years old.Participants must have other neurological or neurocognitive conditions unrelated to stroke, including pre-existing dementia, traumatic brain injury, neurodegenerative disorders, or documented pre-stroke cognitive decline.Participants must be less than 3 months post-stroke.Participants must have severe impairments in language comprehension preventing the understanding of simple instructions, severe motor impairments, or complete dependence in activities of daily living.

### Study setting

The first recruitment phase will take place in a specialized outpatient neurological rehabilitation center in the Community of Madrid, Spain, where both intervention sessions and assessments will be conducted. In subsequent phases, recruitment will be extended to additional outpatient neurological rehabilitation centers within the Community of Madrid. All participating centers will use the same intervention protocol, assessment procedures, facilitator training requirements, and fidelity monitoring procedures to ensure consistency across sites.

### Sample size

The sample size was calculated following recommendations for comparing two means in intervention studies (23). As the Fugl-Meyer Assessment (FMA) was the main outcome, change in this measure was selected as the primary criterion. Following previous research (24), the minimal difference in scores used to detect between-group differences in motor improvement was 4, assuming a standard deviation of 12. Using a two-tailed t-test for the difference between means with 80% power and a 5% level of significance, the sample size required was 70 participants, with 35 per group. Considering a dropout rate of 10%, the final required sample size was estimated at 76 participants, with 38 per group.

Given the specificity of the target population and the outpatient rehabilitation context, recruitment will be conducted in successive phases. The first recruitment phase, conducted in a single center, is expected to include approximately 24 eligible and recruitable participants, with 12 participants per group. Subsequent phases will include additional outpatient neurological rehabilitation centers in the Community of Madrid until the total required sample size of 76 participants is reached. Based on the projected recruitment capacity across participating centers, completion of recruitment is expected within approximately 1 year.

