The main strength of this study lies in its integrative approach, delivered in a real-world outpatient rehabilitation setting. The use of standardized and validated outcome measures across domains will provide relevant data to inform future research and rehabilitation practice.

Nonetheless, the study’s primary aim is to evaluate the effects of the intervention on motor outcomes and to provide preliminary information on its potential role in post-stroke rehabilitation. Although this study is powered to detect clinically significant differences in motor outcomes, it should be interpreted as an initial evaluation of an integrative intervention model.

If the intervention demonstrates favorable results, it could be incorporated as a complementary strategy within multidisciplinary post-stroke rehabilitation programs. Future research should aim to replicate these findings in larger and multicenter studies.

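### The stated inputs (difference 4, SD 12, two-sample t-test) need about 143 per group, not 35; at 35 per group they give about 28% power, not 80%

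*Protocol article*

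**What the plan says.** The Sample size section of the protocol article gives a complete set of inputs:

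- Sizing variable: for the Fugl-Meyer Assessment (FMA), "change in this measure was selected as the primary criterion".
- Effect: "the minimal difference in scores used to detect between-group differences in motor improvement was 4".
- Variability: "assuming a standard deviation of 12". The text does not say which SD this is, and it gives no baseline to follow-up correlation.
- Test: "Using a two-tailed t-test for the difference between means with 80% power and a 5% level of significance".
- Result: "the sample size required was 70 participants, with 35 per group".
- Dropout: "Considering a dropout rate of 10%, the final required sample size was estimated at 76 participants, with 38 per group".

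The Discussion relies on this result: "Although this study is powered to detect clinically significant differences in motor outcomes". The Limitations section also refers to the a priori calculation and names only dropout, clinical variability and recruitment flow as threats to power.

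**The concern.** A difference of 4 with an SD of 12 is a standardised effect of one third. A two-sample comparison of that effect at 80% power needs well over 100 per group, so 35 per group cannot be right for the stated test. All the inputs and the answer stand in one paragraph, so this is a contradiction within the document and not a detail left to an analysis plan.

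What is at stake is how the primary result will be read. A reader told that the trial has 80% power for 4 points may take a non-significant result as evidence that the intervention has no useful motor effect. On the stated inputs, a true 4-point benefit would be missed about 7 times in 10.

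**Working it through.** **Inputs** (all from the Sample size section): difference δ = 4, SD σ = 12, two-sided α = 0.05, power 0.80, 1:1 allocation, two independent means. Standardised effect = 4/12 = 0.333.

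**1. Attempt to reproduce 35 per group.**

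n per group = 2 × (z₀.₉₇₅ + z₀.₈₀)² × (σ/δ)² = 2 × (1.960 + 0.842)² × (12/4)² = 2 × 7.849 × 9 = 141.3, so 142.

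The noncentral t calculation gives 142.2, so 143 per group (286 in total). The stated 35 is not reproduced. A one-sided test would still need 112 per group.

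**2. Where 70 may come from.** Without the factor 2 for two groups, the formula gives 7.849 × 9 = 70.6. That is a one-sample or paired calculation, and it is close to the stated total of 70. The number may have been taken as the two-group total and halved. The document does not say so, so this is inference. The fit is not exact either: 70.6 rounds up to 71, and the exact one-sample t calculation gives 73. An SD of 6, or a difference of 8, would give 36 to 37 per group, but neither is stated.

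**3. Power that the stated inputs deliver** (two-sided two-sample t-test, δ = 4, σ = 12):

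| Evaluable per group | Power |
|---|---|
| 34 (76 less 10%, halved) | 27.3% |
| 35 | 28.0% |
| 38 (no dropout) | 30.0% |

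The normal approximation at 35 per group gives 28.6%.

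**4. What 35 per group could detect with 80% power.**

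- With SD 12: a difference of 8.15, about twice the stated 4. With 38 per group it is 7.8.
- With a difference of 4: only if the SD of the analysed quantity is 5.89.
- Power for 4 points at 35 per group by SD: 79% at SD 6, 54% at 8, 38% at 10, 28% at 12.

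**5. If 12 is a cross-sectional SD.** The document does not say this, so it is an assumption. With baseline to week-5 correlation r, the SD of change is 12 × √(2(1 − r)), and the baseline-adjusted residual SD is 12 × √(1 − r²). Setting each equal to 5.89 gives r ≈ 0.88 for change and r ≈ 0.87 for baseline adjustment. Power at 35 per group for assumed values of r:

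| r | Change score | Baseline-adjusted |
|---|---|---|
| 0.5 | 28% | 35% |
| 0.7 | 43% | 49% |
| 0.8 | 58% | 63% |
| 0.9 | 87% | 88% |

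**6. Dropout.** 70/(1 − 0.10) = 77.8, so 78 (39 per group). Multiplying instead gives 70 × 1.10 = 77. Enrolling 76 and losing 10% leaves 76 × 0.9 = 68.4, or 34.2 per group, which is below 35. Enrolling 76 covers 1 − 70/76 = 7.9% dropout.

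**The case against.** The strongest reply is that 28% is a conditional figure. The document does not say what the SD of 12 describes, and the cited source is not available here. The primary analysis is a linear mixed model that includes the baseline measurement, not the t-test used for sizing. If 12 is the spread of scores at one time point, and baseline and week-5 scores are highly correlated, power could be much higher, up to 87 to 88% at a correlation of 0.9.

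Part of this stands. The 28% belongs to the stated test and inputs and is not a known property of the trial. It does not rescue the paragraph, though. The calculation is set on change, uses a t-test for two means, and invokes neither a correlation nor a reduction in variance. Read plainly, 12 is the SD of change. The rescue needs a correlation of about 0.87 to 0.88, which the document never states or supports.

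Two smaller replies are fair. The origin of the 70 cannot be proved from the text. The dropout gap of two participants is trivial beside a four-fold shortfall. It is also true that the article calls its evidence preliminary and warns that power may be affected. Neither statement corrects the claim of 80% power.

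**Conclusion.** The concern holds. The stated inputs require 142 to 143 per group, about four times the stated 35. With 34 to 38 evaluable per group, the stated test has 27% to 30% power for a 4-point difference, against the 80% claimed. It has 80% power only for about 8.2 points at 35 per group. These figures take 12 as the SD of the quantity compared, namely change in FMA, which is how the section reads. They would improve only under a smaller SD or a high correlation that the document does not give. The claim in the Discussion that the study is adequately powered is unsupported as written. The dropout figure is a separate, minor error. The main point must be fixed before recruitment begins.

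**What to change.** The target of 76 can stay if that is what is feasible, but the text must say what it delivers. Choose one:

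- **(a) Keep SD 12.** State that the trial has about 28% power for 4 points and 80% power for about 8.2 points with 35 evaluable per group. Say openly that sizing for 4 points would need about 286 evaluable participants (286/0.9 = 317.8, so 318 enrolled) if that is not feasible. Present 76 as a feasibility-based number and say that it allows for 7.9% dropout if 70 are to remain.
- **(b) Replace SD 12.** Do this only if the cited source supports an SD of change, or a baseline-adjusted residual SD, near 5.9. Name which SD it is, give its source and show the calculation. The SD must come from the evidence and not be chosen to fit 35 per group. Then correct the inflated total to 78 (39 per group), or state that 76 allows for 7.9% dropout.

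In either case, correct the Sample size paragraph so that inputs, test and result agree. Unless (b) can be shown, delete or qualify the Discussion's statement that the study is powered for clinically significant motor differences, and align the nearby remark that it is primarily powered toward motor outcomes.

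The cost is rewording before recruitment starts and a less favourable power statement. No extra participants are needed, except two if the sponsor takes (b) and raises the total to 78.

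### A 10% dropout allowance on 70 participants gives 78, not 76; the planned 76 leaves about 68 completers, below the plan's own requirement

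*Protocol article*

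**What the plan says.** The protocol article, under Sample size, bases the calculation on the Fugl-Meyer Assessment, comparing two group means with a difference of 4 points and a standard deviation of 12, "with 80% power and a 5% level of significance". It reports that "the sample size required was 70 participants, with 35 per group". It then allows for loss to follow-up: "Considering a dropout rate of 10%, the final required sample size was estimated at 76 participants, with 38 per group". It gives no formula for this step.

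The figure of 76 is the recruitment target. Study design says that recruitment continues "until the planned sample of 76 participants is reached", and Recruitment and the second paragraph of Sample size repeat the same total.

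Under Dropout and missing data management, the primary analysis covers randomised participants who have outcome data. It uses all available repeated measures under a missing-at-random assumption, with no imputation.

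**The concern.** A dropout allowance should leave the required number in the analysis after the assumed losses. The article prints all three quantities (required number, dropout rate, number to enrol), so the step can be checked directly, and the three cannot all hold. Either the dropout rate or the total is misstated.

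At stake is whether the allowance that the plan claims is delivered. Recruitment ends at 76, so at the plan's own dropout rate the trial is expected to finish below the number it says it needs. If the base number is later recalculated and inflated in the same way, the total would again be too small for the stated rate.

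**Working it through.** **Inputs**, all from Sample size: required number after dropout 35 per group (70 in total); dropout 10%; enrolled 38 per group (76 in total).

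**Trying to reproduce 76**

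- Division by (1 − dropout), the correct method: 35/0.90 = 38.9, so 39 per group and 78 in total. On the total, 70/0.90 = 77.8, so 78.
- Multiplication by (1 + dropout), a common shortcut that under-inflates: 35 × 1.10 = 38.5 per group, which rounds up to 39; on the total, 70 × 1.10 = 77.
- 38 per group appears only if 38.5 is rounded down.

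**Working back from 76**

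- Loss that 76 can absorb and still leave 70: (76 − 70)/76 = 6/76 = 7.9%. Per group, (38 − 35)/38 = 3/38 = 7.9%.
- Expected completers at 10%: 76 × 0.90 = 68.4, or 38 × 0.90 = 34.2 per group. The shortfall is 70 − 68.4 = 1.6 completers.

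**Chance of reaching 70 completers.** Treat the number of completers as binomial with retention probability 0.90, assuming that participants drop out independently and that each dropout is lost from the analysis:

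| Enrolled | Expected completers | P(at least 70 completers) |
|---|---|---|
| 76 | 68.4 | 0.353 |
| 78 | 78 × 0.90 = 70.2 | 0.622 |

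**Cost in power.** To isolate this step, take the standardised effect at which 35 per group gives exactly 80% in a two-sided 5% t-test. That effect is 0.679. It is back-solved for this comparison and is not the plan's stated effect.

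| Per group | Power at effect 0.679 (hypothetical) | Power at the stated 4/12 = 0.333 |
|---|---|---|
| 35 | 80.0% | about 28% |
| 34.2 | 79.1% | – |
| 34 | 78.8% | about 27% |

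On either basis the dropout slip costs about one percentage point. The last column also shows that 35 per group does not give 80% power at the stated difference and standard deviation. Those inputs require 142 per group (normal approximation) or 143 (t-test). That is a separate error in the base number and is not needed for the present point.

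**The case against.** The strongest reply is that the gap is trivial. It is two participants, on an allowance that is itself approximate. Randomization and allocation specifies simple randomisation, under which the size of one arm out of 76 has a standard deviation of √(76 × 0.5 × 0.5) ≈ 4.4, so one more or fewer per group is well inside ordinary variation. The origin of 38 may be no more than 38.5 rounded down. This stands as a statement about size, and it is why the point is minor. It does not make the figures agree: a required sample size is rounded up, and neither method of inflation then gives 38.

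A second reply is that completers are not the analysis set. The mixed model uses all available data, so a participant who leaves after week 5 still informs the between-group comparison, and the article does not say to which time point the 10% refers. This also stands in part. It softens the practical loss, and the binomial probabilities above are pessimistic to that extent. But the article itself adds the allowance to protect 70, and 76 does not do that at 10%.

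A third reply is that the correction is beside the point because 70 is itself wrong. With a difference of 4 and a standard deviation of 12, 39 per group would give only about 31% power even with no dropout. That is true and far more important. It means that 78 must not be read as restoring 80% power. The two errors are independent, however, and correcting the base would not by itself correct the inflation step.

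**Conclusion.** The concern holds. With 70 required and 10% dropout, the number to enrol is 78 (39 per group). The stated 76 corresponds to 7.9% dropout and leaves about 68 expected completers at 10%. The shortfall is two enrolled participants or 1.6 expected completers, worth about one percentage point of power.

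The mismatch needs no assumption beyond the article's own three figures, and no other section corrects it. Only the 35% and 62% probabilities rest on independent dropout and on complete loss of each dropout from the analysis. Only the 79–80% power figures rest on the hypothetical effect of 0.679; they do not describe the trial's actual power. This is a minor inconsistency to correct, not a threat to the trial in its own right.

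**What to change.** In Sample size, make the dropout rate and the total agree by dividing the required number by (1 − dropout). There are two ways to do this:

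- **Keep 76.** State that it allows for about 8% dropout, or that at 10% about 68 participants (34 per group) are expected to be evaluable, and give the power at that number. This takes one sentence and no extra participants. The stated figure becomes slightly less favourable.
- **Keep 70 and 10%.** Change the total to 78 (39 per group) in Study design, Recruitment and Sample size. This takes two more participants.

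Make the change together with a review of the base number, because any power quoted from the stated difference of 4 and standard deviation of 12 would be about 27% at 34 per group. Apply the same division to whatever base results. For example, 142/0.90 = 157.8 gives 158 per group, and 143/0.90 = 158.9 gives 159. Study status says that recruitment has not begun, so the text can be corrected before anyone is enrolled.
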